### 2.6. Statistical Analysis

An a priori sample size estimation was performed using G*Power software version 3.1.9.7 [36]. The calculation was based on the primary outcome (CAR), assuming a one-tailed test, a type I error (α) of 0.05, a statistical power (1−β) of 0.80, and a medium expected effect size. Based on these assumptions, the estimated sample size is 102 participants (51 per group).

The data collected will be pseudonymized (a technique that modifies and masks personal and sensitive data of a natural person to prevent direct or easy attribution to the individual) and will be used exclusively for the purposes of the Wear-Smile study project.

Statistical analyses will be performed according to the intention-to-treat (ITT) principle. Per-protocol analyses will additionally be conducted as sensitivity analyses.

The statistical analysis will be applied to analyze continuous and categorical variables, with particular attention to the handling of missing data and the analysis of both intra- and inter-subject variability.

To enhance data interpretation and understanding of distributions, graphical representations such as histograms, boxplots conditioned on the target variable, and scatter plots will be employed.

To minimize the risk of bias due to missing data, a missing data analysis will be performed to assess whether data are Missing Completely at Random (MCAR) or dependent on other variables. If missing data exceeds 5%, it will be handled using multiple imputation techniques based on appropriate statistical models, thereby reducing the risk of bias.

The adoption of these methodologies will strengthen the scientific evidence regarding the effectiveness of telerehabilitation for smoking cessation, optimize result interpretation, and provide valuable insights for future clinical implementations and public health policies.

A sensitivity analysis will be conducted to compare results between the original datasets and the imputed datasets.

Statistical analyses will be performed using SPSS version 28.0, R version 4.2, or STATA version 17.0. The level of statistical significance will be set at *p* < 0.05 for all tests, with Bonferroni correction applied for multiple comparisons to control the risk of Type I error. Effect sizes and 95% confidence intervals (95% CI) will also be reported whenever appropriate.

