Before performing inferential analyses, an Exploratory Data Analysis (EDA) will be conducted to describe the characteristics of the sample and to identify any anomalies or patterns in the data.

Continuous variables will be presented as mean and standard deviation (SD) for normally distributed data and as median and interquartile range (IQR) for non-normally distributed data. Categorical variables will be reported as frequencies and percentages. The Shapiro–Wilk test will be used to assess the normality of distributions and determine the appropriate use of parametric or non-parametric tests.

Longitudinal changes in primary and secondary outcomes over time (baseline, 6 months, and 12 months) will additionally be analyzed using mixed-effects regression models accounting for repeated measurements within participants.

Comparisons between the intervention group (telerehabilitation using the integrated telemedicine platform and wearable remote-monitoring devices) and the control group (standard multimodal behavioral-psychological treatment without telemedicine or wearable devices) will be performed using Student’s t-test for normally distributed continuous variables and the Mann–Whitney U test for non-normally distributed variables.

Within-group longitudinal comparisons across follow-up assessments will be performed using paired Student’s t-tests or Wilcoxon signed-rank tests, as appropriate according to data distribution.

Comparisons between categorical variables, including smoking cessation status (abstinent/non-abstinent), will be performed using the Chi-square test or Fisher’s exact test when appropriate.

Associations between the intervention and both primary and secondary outcomes will be explored using Pearson’s correlation coefficient for normally distributed variables and Spearman’s rank correlation coefficient for non-normally distributed variables.

To control for potential confounding factors (e.g., age, gender, comorbidities), multivariate linear regression models will be applied. In addition, multiple logistic regression will be used to identify predictors of successful smoking cessation. The dependent variable will be smoking cessation status (yes/no), and the independent variables will include type of nicotine use (combustible tobacco vs. HTP vs. ENDS), age, gender, motivation, dependence severity, and comorbidities.

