Pre-specified subgroup analyses will be performed according to the type of nicotine-containing product used (combustible tobacco cigarettes, heated tobacco products, and electronic nicotine delivery systems), dependence severity, and motivation to quit. In addition, the type of nicotine-containing product will be included as a covariate in multivariable regression models to account for its potential confounding effect on smoking cessation outcomes.

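### Continuous outcomes are compared between arms without their collected baseline values, and no regression model is stated to contain randomised arm: lost efficiency, not bias

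*Protocol article*

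**What the plan says.** All of this is in Section 2.6 of the protocol article unless stated otherwise.

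- **Continuous outcomes, between arms:** Student's t-test or the Mann-Whitney U test, chosen by distribution. Neither a baseline covariate nor a change score is mentioned.
- **Continuous outcomes, within arm:** "Within-group longitudinal comparisons across follow-up assessments will be performed using paired" t-tests or Wilcoxon signed-rank tests.
- **Longitudinal models:** mixed-effects regression for primary and secondary outcomes over baseline, 6 and 12 months, introduced as an additional analysis. No arm or arm-by-time term is stated.
- **Abstinence, between arms:** Chi-square or Fisher's exact test, unadjusted.
- **Confounders:** "To control for potential confounding factors (e.g., age, gender, comorbidities), multivariate linear regression models will be applied". No outcome is named for these models.
- **Logistic model:** its stated purpose is to find predictors of quitting, and "the independent variables will include type of nicotine use (combustible tobacco vs. HTP vs. ENDS), age, gender, motivation, dependence severity, and comorbidities". Arm is not in the list.
- **Subgroup paragraph:** "the type of nicotine-containing product will be included as a covariate in multivariable regression models" for cessation outcomes. Neither the type of model nor an arm term is given.

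Section 2.5.2 and Table 1 show that nicotine dependence (FTND), SF-36, OHIP-14, probing depth and the bleeding index are all measured at baseline. Section 2.5.2 adds the motivation test.

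**The concern.** In a trial of 102 people, the baseline value is usually the strongest predictor of the same measure at follow-up. A two-sample test on follow-up values leaves that variation in the error term. Within-arm paired tests do use baseline, but they do not estimate the difference between arms.

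Several analyses could each be read as the between-arm result for a continuous outcome: the t-test or its rank alternative, the mixed model and the linear regression. The article does not say which one leads. For abstinence it plans regression and adjustment, yet it states no model as containing arm, so it is unclear which model would give an adjusted treatment effect. At stake are power on the secondary outcomes and freedom to choose among analyses once results are seen.

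**Working it through.** **1. The plan's own sample size.** Inputs from Section 2.6: "assuming a one-tailed test", "a type I error (α) of 0.05", "a statistical power (1−β) of 0.80", "and a medium expected effect size". No number is attached to the effect; I take it as d = 0.5. For a two-sample t-test with n per arm, the noncentrality is d√(n/2) on 2n − 2 degrees of freedom. At n = 51 it is 0.5 × √25.5 = 2.525, and one-sided power is 0.806. The smallest n that reaches 0.80 is 51, so the total is 102, as stated. The sample size is not in question here.

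**2. What baseline is worth for a continuous outcome.** Adjusting for a baseline that has correlation r with follow-up multiplies the residual variance by 1 − r². In the normal approximation, two-sided power at 0.05 is Φ(0.5√25.5 / √(1 − r²) − 1.96). The article gives no r, so a range is shown. The last column, 51 × (1 − r²), is the number per arm at which the adjusted analysis matches the unadjusted one with 51.

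| r (assumed) | 1 − r² | 2.525/√(1 − r²) | Two-sided power | One-sided power | Equivalent n per arm |
|---|---|---|---|---|---|
| baseline not used | 1 | 2.525 | 0.714 | 0.811 | 51 |
| 0.3 | 0.91 | 2.647 | 0.754 | 0.842 | 46.4 |
| 0.5 | 0.75 | 2.915 | 0.830 | 0.898 | 38.3 |
| 0.7 | 0.51 | 3.536 | 0.942 | 0.971 | 26.0 |

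The two-sided gain runs from 4 points (0.754 − 0.714) to 23 points (0.942 − 0.714).

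If the t-test were meant for change from baseline, the variance factor would be 2(1 − r). Two-sided power would then be 0.569, 0.714 and 0.903 at r = 0.3, 0.5 and 0.7, below the adjusted analysis each time.

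**3. What covariates are worth for abstinence.** Everyone smokes at entry, so baseline abstinence is constant and cannot be used for adjustment. Other covariates can. All inputs in the two simulations below are assumptions; tests are two-sided at 0.05 with 51 per arm.

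*One covariate* (intercept −1.5, arm log-odds ratio 1.2, one standard-normal covariate, 3,000 trials per setting):

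| Covariate log-OR per SD | Unadjusted test | Logistic, arm + covariate |
|---|---|---|
| 0 | 0.79 | 0.78 |
| 0.7 | 0.72 | 0.75 |
| 1.2 | 0.61 | 0.70 |

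*Larger set* (FTND, motivation and three-level product split 60/20/20; intercept −1.9, arm log-odds ratio 1.25; 2,000 trials; unpenalised Wald test):

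| Covariate strength (log-OR) | Unadjusted test | Logistic, arm + set |
|---|---|---|
| none prognostic | 0.734 | 0.706 |
| FTND and motivation 0.3 each | 0.732 | 0.725 |
| one at 0.5 | 0.689 | 0.692 |
| two at 0.5, product 0.3 | 0.688 | 0.714 |

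At these strengths the larger set ranges from a loss of about 3 points to a gain of about 3. Gains of about 5 and 10 points need log-odds ratios of 1.0 and 1.5.

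**4. Room for covariates in the logistic model.** The listed variables take at least 2 (product) + 1 + 1 + 1 + 1 + 1 = 7 parameters, or 8 with arm. The article gives no abstinence rate. At an assumed 15% there are 0.15 × 102 = 15.3 events, and at 25% there are 25.5. That is 15.3/8 = 1.9 to 25.5/8 = 3.2 events per parameter. Arm plus two single-parameter covariates gives 15.3/3 = 5.1 to 25.5/3 = 8.5.

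**The case against.** The strongest reply has four parts.

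1. **The unadjusted tests are valid.** Allocation is 1:1, random and concealed, so type I error already allows for chance imbalance. This stands. A reader might infer that the Chi-square test on abstinence is deficient or biased; the documents do not support that.

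2. **Adjusted models are planned.** A reader might conclude that the trial will produce no efficient adjusted treatment effect, or that the logistic model is the only one for cessation. Neither follows. The mixed models cover primary and secondary outcomes with baseline as a time point, and the subgroup paragraph plans multivariable models for cessation outcomes. With an arm-by-time term, the mixed model would recover the baseline information for continuous outcomes. What remains is that the article states no such term and puts this model second to the two-sample tests.

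3. **The logistic and linear models are not what they may seem.** The logistic model is declared a search for predictors, and its list is not worded as exhaustive. The linear-regression sentence names no outcome, and the next sentence assigns logistic regression to the yes/no outcome. Reading it as linear regression on abstinence goes beyond the text. It needs a clarification, not a correction.

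4. **Model terms belong in an analysis plan.** One may exist that is not shown, and the missing arm-by-time term alone would be no finding. But the article itself fixes the between-arm tests for continuous outcomes and ranks the mixed model as additional. Filling in terms elsewhere would not change that order.

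**Conclusion.** The point holds as a matter of efficiency and specification. For continuous outcomes with a baseline value, the between-arm tests named in the article give up about 4 to 23 points of two-sided power at 51 per arm and d = 0.5, across assumed baseline correlations of 0.3 to 0.7. These figures use a normal approximation with full follow-up. The protocol supplies neither the correlations nor a numerical effect size for these outcomes.

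For abstinence the case is weaker. The gain from adjustment is uncertain, from a small loss to a few points at moderate covariate strength, and events will probably be few. That does not justify replacing Chi-square or Fisher as the main analysis. It does support a small logistic model that contains arm, as a supporting analysis.

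This should be changed, but it does not threaten the validity of the planned comparisons.

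**What to change.** **Continuous outcomes measured at baseline.** Name one between-arm analysis: the mixed model already planned, with arm, time and arm-by-time, adjusted for or constrained on baseline; or ANCOVA at each follow-up. Make the t-test, Mann-Whitney and within-arm paired tests descriptive. Outcomes with no baseline, such as satisfaction, can keep a two-sample comparison.

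**Abstinence.** Keep Chi-square or Fisher, reported with a risk difference and 95% confidence interval. Add a supportive logistic model with arm and one or two pre-specified baseline covariates, for example FTND, with Firth's penalty if events are few. Do not simply add arm to the existing list. The predictor model can stay, labelled exploratory.

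**Linear models.** State that they apply to continuous outcomes only.

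**Cost.** A change of wording. The baseline data are already to be collected, and Section 2.7 says enrolment has not started. The downside is slightly more modelling work and reliance on model assumptions, which matters most for skewed outcomes.

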### 2.7. Trial Status

At the time of study protocol submission, the Wear-Smile project is in the pre-recruitment phase, and participant enrollment has not yet started.

The SPIRIT 2025 participant timeline template [24] was compiled in Table 1 to outline the schedule of enrollment, interventions, and assessments.

## 3. Discussion

The present study protocol describes the design and methodology of the Wear-Smile project, a multidisciplinary smoking cessation program integrating telemedicine and wearable remote-monitoring technologies into a rehabilitation pathway for persons who smoke combustible tobacco, heated tobacco products, and electronic nicotine delivery systems.

Tobacco smoking remains one of the leading preventable causes of morbidity and mortality worldwide and represents a major modifiable risk factor for chronic non-communicable diseases, including cardiovascular diseases, respiratory disorders, oral diseases, and malignant neoplasms [2,37].

In addition to physical consequences, smoking behavior is closely interconnected with psychological well-being, anxiety, depression, and social determinants of health [38]. Consequently, smoking cessation should not be considered exclusively a behavioral intervention but rather a comprehensive multidimensional healthcare strategy requiring collaboration among different healthcare providers.

The Wear-Smile project was conceived within this multidimensional framework. The integration of cardiology, pulmonary, dental, and psychological expertise may contribute to a more holistic management of persons who smoke, particularly in patients with multiple comorbidities due to tobacco. The concept of frailty is increasingly relevant in contemporary healthcare systems due to population aging and the growing prevalence of chronic diseases associated with modifiable risk factors such as tobacco use [39,40]. Fragile individuals often require continuous monitoring, multidisciplinary care, frequent healthcare access, and long-term therapeutic adherence, representing a major challenge for healthcare sustainability [41,42]. In this context, telemedicine and wearable monitoring technologies may offer valuable opportunities to improve continuity of care, patient engagement, remote monitoring, and healthcare accessibility.

Recent advances in wearable technologies and integrated telemedicine systems have expanded the potential applications of remote healthcare across several medical fields [43,44]. Wearable monitoring devices may facilitate continuous longitudinal assessment of physiological parameters while simultaneously promoting patient empowerment and self-awareness regarding health behaviors [45]. In smoking cessation programs, these technologies may additionally improve adherence to rehabilitation pathways [45].

Despite the increasing diffusion of telemedicine interventions for smoking cessation, many available interventions are limited to isolated digital tools, such as mobile applications or messaging systems, without implementing a truly integrated multidisciplinary rehabilitation model [16,46]. The Wear-Smile project was designed to address these limitations by combining wearable physiological monitoring, telemedicine-assisted multidisciplinary care, and longitudinal assessment of cardiopulmonary, oral, psychological, and quality-of-life outcomes.

Although telemedicine and wearable technologies offer important opportunities to improve access to multidisciplinary smoking cessation services, their implementation should also be considered from a health equity perspective. Digital health interventions have the potential to reduce geographical barriers and improve continuity of care, particularly for individuals living in remote or underserved areas [47,48,49]. However, these benefits may not be equally distributed across the population. Differences in socioeconomic status, educational level, digital literacy, internet connectivity, and access to technological resources may influence both participation in telemedicine-based interventions and long-term engagement with digital health solutions. Consequently, individuals with fewer economic or technological resources may be underrepresented in digital healthcare programs, potentially limiting the generalizability of study findings and widening existing health disparities. [47,48,49]. In the present study, participants allocated to the control group will be required to have access to home monitoring devices for the scheduled home assessments. This requirement may limit participation among individuals with fewer economic resources and should therefore be considered when interpreting the external validity and generalizability of the findings. Nevertheless, identifying these practical challenges may provide valuable information for the future development of more equitable telemedicine-based smoking cessation programs. Future large-scale studies should aim to reduce barriers to participation by ensuring broader access to monitoring technologies and digital health resources, thereby promoting more equitable implementation of multidisciplinary telemedicine interventions [48,49].

Another relevant strength of the present protocol is the inclusion of persons who smoke different nicotine-containing products, including combustible tobacco, heated tobacco products, and electronic nicotine delivery systems. This aspect may improve the external validity and generalizability of the findings, considering the increasing global diffusion of alternative nicotine delivery products and the ongoing debate regarding their long-term health effects and role within smoking cessation pathways [50].

The present protocol additionally aims to investigate patient-centered outcomes, including usability, treatment acceptability, adherence, and satisfaction with telemedicine-assisted rehabilitation. These aspects are important because two previous umbrella reviews focusing on the use of technology in smoking cessation programs have highlighted a marked lack of data on acceptability and satisfaction [16,51]. Furthermore, low adherence and limited accessibility have been frequently reported as barriers to traditional smoking cessation services [52]. Telemedicine-based interventions may reduce geographical, organizational, and time-related barriers while improving flexibility and continuity of specialist support [53].

Nevertheless, some limitations of the study should be acknowledged. Due to the nature of the intervention, blinding of participants and healthcare providers is not feasible, potentially increasing the risk of performance bias. Smoking abstinence outcomes will primarily rely on self-reported measures, which may introduce reporting bias. In addition, monocentric design may limit the generalizability of the results to different healthcare settings and populations. Potential variability in digital literacy and technological confidence among participants may also influence adherence to wearable device utilization and engagement with telemedicine platforms. Differences in participants’ acceptance of digital health technologies and their long-term engagement with wearable devices may further affect adherence to the intervention and contribute to attrition bias.

To mitigate these risks related to technology adoption and participant engagement, participants allocated to the intervention group will receive standardized training on the use of the telemedicine platform and wearable devices, together with ongoing technical support throughout the study. Furthermore, adherence to the intervention and device utilization will be monitored during follow-up visits to identify potential barriers to engagement. Differential engagement between the intervention and control groups may also represent a potential source of bias and will be considered when interpreting the study findings and conducting sensitivity analyses.

Despite these limitations, the Wear-Smile project may provide important preliminary evidence regarding the feasibility, acceptability, and potential effectiveness of integrating telemedicine and wearable remote-monitoring devices into multidisciplinary smoking cessation programs. If demonstrated to be effective, this model may contribute to improving smoking abstinence rates, reducing smoking-related morbidity, enhancing quality of life, and optimizing healthcare resource utilization. Moreover, the implementation of integrated telemedicine pathways may facilitate stronger collaboration networks among healthcare professionals involved in smoking cessation and chronic disease prevention.

Future multicenter studies with longer follow-up periods will be necessary to further validate the findings and evaluate the long-term sustainability and cost-effectiveness of telemedicine-assisted smoking cessation interventions in different clinical and healthcare contexts.

## 4. Conclusions

The Wear-Smile project introduces a multidisciplinary smoking cessation rehabilitation program integrating telemedicine and wearable remote-monitoring technologies for persons who smoke combustible tobacco, heated tobacco products, and electronic nicotine delivery systems.

The protocol was designed to address the multifactorial nature of tobacco dependence through the collaboration of cardiologists, pulmonologists, dentists, and psychological specialists to improve smoking cessation outcomes and promote a more patient-centered approach to care.

The integration of wearable monitoring devices and an interactive telemedicine platform may enhance continuity of care, remote monitoring, patient engagement, and adherence to rehabilitation programs while reducing organizational and geographical barriers frequently associated with conventional smoking cessation services. Furthermore, the longitudinal evaluation of cardiopulmonary, oral health, psychological, and quality-of-life outcomes may contribute to a broader understanding of the multidimensional effects of smoking cessation interventions.

The Wear-Smile protocol may provide important preliminary evidence regarding the feasibility and clinical applicability of telemedicine-assisted smoking cessation pathways. If demonstrated to be effective, this integrated model may contribute to improving long-term smoking abstinence, reducing smoking-related morbidity, optimizing healthcare resource utilization, and strengthening multidisciplinary collaboration in preventive healthcare.

